## Definition of an Adverse Event (AE)

An AE can therefore be any unfavourable and unintended sign (including an abnormal laboratory finding), symptom, or disease (new or exacerbated) temporally associated with the use of a medicinal product, whether or not considered related to the medicinal product. For marketed medicinal products, this also includes failure to produce benefits (i.e. lack of efficacy), abuse or misuse.

Examples of an AE **include**:

- Acute episode of psychosis
- Exercise induced injury or complaint

Examples of an AE **do** **not include** a/an:

- Medical or surgical procedure (e.g. endoscopy, appendectomy); the condition that leads to the procedure is an AE.
- Situations where an untoward medical occurrence did not occur (social and/or convenience admission to hospital).

In this study, AEs may include pre- or post-intervention events that occur as a result of protocol-mandated procedures (i.e. invasive procedures, modification of participants’ previous therapeutic regimen).

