Community Care Units (CCU’s) are residential rehabilitation units for people with SMI (predominantly schizophrenia and related psychoses) offering 24-hour intensive multidisciplinary support (30) to people who are typically admitted with treatment resistance and functional disability (31). CCU’s aim to deliver evidence-based rehabilitation interventions that improve independent functioning across a range of health domains (32). Acknowledging the recent expansion of rehabilitation aims for people with schizophrenia to include physical health interventions; understanding the differential impact of exercise types on mental health and functional outcomes in rehabilitation settings is important (33, 34).

Previous research in residential rehabilitation settings revealed feasibility and improvements in functional fitness following implementation of a supervised exercise interval circuit program comprising aerobic interval training involving both aerobic, body weight and resistance elements (24). Overall program acceptability was high, with resistance elements being a preferred component by participants of that program.

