# Study Design

This study will be conducted as a single blind exploratory randomised controlled trial. Participants will be randomised to a supervised resistance training (RT) program or a supervised moderate intensity aerobic interval intervention (AIT), matched for volume and intensity, with the aim to compare RT with AIT with respect to our primary outcome (feasibility) in people with chronic psychotic disorders undergoing psychiatric rehabilitation.

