## 4.4 Screening assessment

Researchers will work with senior nursing staff of three CCU’s for a 3-week period prior to the intervention start date to identify those residents who might meet criteria for the study. After verbal consent is provided, an assessment of inclusion/exclusion criteria will commence. Participants who meet all inclusion criteria and none of the exclusion criteria will be invited to participate in the study and the formal consent process will commence. For those who consent to participate, they will be enrolled in the study and randomized.

Prior to randomisation, all participants recruited to the study will be assessed for baseline characteristics regarding: primary and secondary mental health diagnosis using DSM V by the Consultant psychiatrist on the research team, a range of sociodemographics (age, gender, employment, education, income, ethnicity), medication use – number and type of medications and chronic health conditions. Doses of antipsychotics will be converted to chlorpromazine equivalents using standardised measures (39).

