### Adverse Events

Data on adverse events in both conditions will be reported, including any new injuries, exacerbations of pre-existing conditions, participant withdrawal and reasons and adverse events judged to be as a direct result of the intervention will be specifically recorded in the case report form. We will examine adverse events at before and after each training session. All adverse events reported between consent and final visit will be recorded in the case report form (CRF). The investigator or AEP will ask the Participant non-leading questions in an effort to detect adverse events e.g. “How have you been over since the last session”. We expect that adverse events will occur during the study related to fluctuations in the underlying mental disorder and medications and adjustment to increased physical activity.

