## Definition of a Serious Adverse Event (SAE)

A serious adverse event is any untoward medical occurrence that, at any dose:

a) results in death

b) is life threatening

c) requires hospitalisation or prolongation of an existing hospitalisation.

d) results in disability/incapacity, or

f) Any event deemed by the investigator as being a significant medical event.

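### Section 8.1 defines adverse events by use of a medicinal product, including lack of efficacy, in an exercise trial with no study drug, so the AE rule names the wrong exposure and is over-inclusive

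*Protocol*

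**What the plan says.** The opening of section 8 makes the investigator responsible for documenting events that meet the definitions given in the protocol, so section 8.1 governs. Its general rule covers unfavourable signs, symptoms or diseases "temporally associated with the use of a medicinal product, whether or not considered related to the medicinal product". The next sentence widens it: "For marketed medicinal products, this also includes failure to produce benefits (i.e. lack of efficacy), abuse or misuse". The examples then include "Exercise induced injury or complaint", and a closing sentence admits events arising from procedures that the protocol requires.

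The same vocabulary recurs nearby. Section 8.2 begins "A serious adverse event is any untoward medical occurrence that, at any dose". Section 8.5.2 asks for the causal relationship to the study product, although each of its categories is worded in terms of the study intervention.

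Section 6.1.1 describes AE data for both exercise conditions, "including any new injuries, exacerbations of pre-existing conditions, participant withdrawal and reasons", with separate recording of events judged to result directly from the intervention. Section 11.4 compares AE rates between the two exercise groups and does not restrict them to related events.

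**The concern.** Study Design (section 3) allocates participants to RT or AIT and to nothing else. The exposure named in the AE rule is therefore not one that the trial studies. The only medicinal products in view are those the participants already take, antipsychotics among them: section 4.4 states that "Doses of antipsychotics will be converted to chlorpromazine equivalents using standardised measures". Applied to those marketed drugs, the lack-of-efficacy sentence turns persistent illness into an adverse event. The Introduction describes residents of these units as "typically admitted with treatment resistance and functional disability", so the condition could be common, and section 8.3 starts recording at consent.

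At stake is what the AE rate in section 11.4 measures. If it includes background drug non-response, it is a poorer description of how well each form of exercise is tolerated, and a difference between arms is harder to see.

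**Working it through.** No figure in the plan can be reproduced here: the protocol states no AE rate, threshold or power for adverse events. The check sets the sections side by side.

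1. **Exposure.** Section 3: RT or AIT. Section 8.1: a medicinal product. These do not match.
2. **Reach of the lack-of-efficacy sentence.** The general rule limits diseases to those that are new or exacerbated. The sentence on marketed products adds a further category, and that limit does not clearly carry over to it. Long-standing non-response is therefore not plainly excluded. The text does not name antipsychotics; applying the sentence to them is an inference from sections 1 and 4.4.
3. **Link to exercise elsewhere.** The injury example and the required-procedures sentence in 8.1, the checks before and after each session and the direct-result recording in 6.1.1, and the causality assessment of every event against the intervention in 8.5.2 all tie events to RT or AIT. Exercise events are not lost.
4. **Use in the analysis.** Section 11.4 compares AE rates without a relatedness filter, so the attribution made under 8.5.2 does not remove background events from the count being compared.

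**Illustration of the direction of the effect (all event counts assumed).** Take 25 per arm (section 11.3), one exercise-related event in 3 RT and 1 AIT participants, and independently one background event in a share p of each arm.

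- Mean events per participant, exercise only: 3/25 = 0.12 and 1/25 = 0.04; difference 0.08.
- With p = 0.5: 0.62 and 0.54; difference 0.62 − 0.54 = 0.08, unchanged.
- Variance per participant, exercise only: 0.12 × 0.88 = 0.1056 and 0.04 × 0.96 = 0.0384, sum 0.144. Standard error of the difference: √(0.144/25) = 0.076.
- Background events add p(1 − p) to each arm. With p = 0.5 the sum is 0.144 + 2 × 0.25 = 0.644, and the standard error is √(0.644/25) = 0.161, which is 2.1 times as large.
- With p = 0.1 or 0.9 the sum is 0.144 + 2 × 0.09 = 0.324, and the standard error is √(0.324/25) = 0.114, which is 1.5 times as large.
- With p = 0 or 1 nothing is added.

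Under these assumptions the difference in means is not biased. Its precision falls by a factor between 1 and 2.1, depending on p, which the document does not give.

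**The case against.** The strongest reply is that this is leftover template wording with little practical effect. After baseline, the questions in sections 6.1.1 and 8.3 ask about health problems since the last visit or session; none assesses drug efficacy, so stable non-response may seldom be written down. Section 6.1.1 also expects events from fluctuations in illness and medication, which means change and not persistence. The dose and product phrases in 8.2 and 8.5.2 have no shown operational consequence. All of this stands, and it limits the likely size. It does not make the governing rule right: an investigator who follows 8.1 as written may count events that the trial has no reason to count.

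Three stronger readings are tempting, and the document does not support them.

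- A reader might infer that adverse events are not tied to RT or AIT at all. That is true only of the general sentence in 8.1. The examples in that section, together with 6.1.1 and 8.5.2, supply the link.
- A reader might infer that the three units will count different events because 6.1.1 has a different scope. Its list is introduced as non-exhaustive, it then requires all reported events to be recorded, and section 8 governs. Nothing shows that sites would diverge.
- A reader might infer that a real difference would be largely hidden. On the assumed counts, with p = 0.5, the participants affected would be 25 × (1 − 0.5 × 0.88) = 14.0 against 25 × (1 − 0.5 × 0.96) = 13.0, a ratio of 1.08 where exercise events alone give 3.0. That fall depends on a ratio of affected participants, which section 11.4 does not name; it specifies t-tests or Mann-Whitney tests. The difference in mean events is unchanged.

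**Conclusion.** The point holds in a limited form. Section 8.1 names an exposure that the trial does not study and admits lack of efficacy of marketed drugs, which read literally covers non-response to participants' own medication. The consequence is an over-inclusive AE count and a noisier comparison in section 11.4. How much noisier cannot be determined from the document. The conclusion rests on a literal reading of 8.1 and on the inference that the marketed products concerned are participants' own drugs; the size also depends on how often staff would record non-response.

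The importance is moderate. The primary outcome is recruitment, retention and participation; AE rates are a supporting comparison in an exploratory trial of 50 participants, and no decision threshold depends on them. Correction is still worthwhile because the error lies in the rule itself and is simple to remove.

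**What to change.** - **Section 8.1:** restate the definition as any untoward medical occurrence, new or worsened from baseline, from consent to the final visit, whether or not related to RT, AIT or a study assessment. Delete the medicinal-product and lack-of-efficacy wording.
- **Sections 8.2 and 8.5.2:** replace the dose and study-product phrases with reference to the study intervention.
- **Section 6.1.1:** refer to this single definition, and report withdrawals and their reasons under participant disposition.

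The cost is a protocol amendment. Section 16.7 treats any change as one and requires ethics committee approval before it is implemented. The case report form wording should be checked against the new definition. Psychiatric worsening during the study would still be counted, as it should be in a definition that does not depend on relatedness; the causality assessment in 8.5.2 then separates it from exercise-related events.

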## Definition of a Serious Adverse Event (SAE)

A serious adverse event is any untoward medical occurrence that, at any dose:

a) results in death

b) is life threatening

c) requires hospitalisation or prolongation of an existing hospitalisation.

d) results in disability/incapacity, or

f) Any event deemed by the investigator as being a significant medical event.

## Time Period, Frequency, and Method of Detecting AEs and SAEs

All adverse events will be recorded between the time of consent and the follow-up visits. Each Participant will be monitored regularly by the investigator and study personnel for adverse events occurring throughout the study. The research team will enquire about AEs by asking the following non-leading questions:

At the beginning and post intervention participants will be asked:

*“How are you feeling?” Does your current intervention cause you regular side effects? Do you have any general health conditions that cause you problems on a regular basis (e.g. that we might expect to occur over the duration of this study?"*

At subsequent scheduled visits, participants will be asked:

*“Since your last visit, have you had any health problems?”*

## Recording of AEs and SAEs

If an AE/SAE occurs during the course of the intervention the Investigator/delegated research staff will report accordingly with immediate medical attention sought as per usual CCU guidelines for the safe prescription of exercise within the facilities and record all relevant information regarding an AE/SAE in to the CRF. Exercise may be able to be modified to allow continued participation in the program for any minor injuries or exacerbations of pre-existing conditions, following review by a General Practitioner and with the consent and agreement of the participant and research team (and as per usual exercise injury management policy of the CCU).

## Evaluating AEs and SAEs

### Assessment of Intensity

The investigator will make an assessment of intensity for each AE and SAE reported during the study. The assessment will be based on the investigator’s clinical judgement. The intensity of each AE and SAE recorded in the CRF should be assigned to one of the following categories:

**Mild:** An event that is easily tolerated by the Participant, causing minimal discomfort and not interfering with everyday activities.

**Moderate:** An event that is sufficiently discomforting to interfere with normal everyday activities.

**Severe:** An event which is incapacitating and prevents normal everyday activities.

An AE that is assessed as severe should not be confused with an SAE. Severity is a category utilised for rating the intensity of an event; and both AEs and SAEs can be assessed as severe. An event is defined as “serious” when it meets one of the pre-defined outcomes as described in Section 8.2 “Definition of an SAE”.

### Assessment of Causality

The investigator is obligated to assess the relationship between the intervention and the occurrence of each AE/SAE. The investigator will use clinical judgment to determine the relationship. Alternative causes, such as natural history of the underlying diseases, concomitant therapy, other risk factors, and the temporal relationship of the event to the intervention will be considered and investigated.

The causal relationship to the study product assessed by the Investigator (or medically qualified delegate) should be assessed using the following classifications:

**Not Related** In the Investigator’s opinion, there is not a causal relationship between the study intervention and the adverse event.

**Unlikely** The temporal association between the adverse event and study intervention is such that the study intervention is not likely to have any reasonable association with the adverse event.

**Possible** The adverse event could have been caused by the study Participant’s clinical state or the study intervention.

**Probable** The adverse event follows a reasonable temporal sequence from the time of study intervention, abates upon discontinuation of the study intervention and cannot be reasonably explained by the known characteristics of the study Participant’s clinical state.

**Definitely** The adverse event follows a reasonable temporal sequence from the time of study intervention or reappears when study intervention is reintroduced.

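### The two top adverse-event causality grades are inverted as written: Definitely is easier to meet than Probable

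*Protocol*

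**What the plan says.** Section 8.5.2 (Assessment of Causality) offers five grades, from *Not Related* up to *Definitely*.

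- *Probable* has three conditions that must hold together. The first is a reasonable time sequence. The event must also be one that "abates upon discontinuation of the study intervention and cannot be reasonably explained by the known characteristics" of the participant's clinical state.
- *Definitely* has two conditions joined as alternatives: "The adverse event follows a reasonable temporal sequence from the time of study intervention or reappears when study intervention is reintroduced".

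The text before the grades says "The investigator will use clinical judgment to determine the relationship". It adds that alternative causes, including the natural history of the underlying disease, will be considered. It then directs that causality be assessed with the listed classifications.

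Section 6.1.1 (Adverse Events) gives relatedness a use: "adverse events judged to be as a direct result of the intervention will be specifically recorded in the case report form". The same section anticipates background events: it expects that "adverse events will occur during the study related to fluctuations in the underlying mental disorder and medications".

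**The concern.** An ordered causality scale works only if each step up asks for more evidence. Here the last step asks for less. The two conditions that separate an exercise effect from coincidence, abatement on stopping and exclusion of the clinical state, belong to *Probable* and are absent from *Definitely*.

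This matters in this population because the protocol itself expects events driven by the illness and by medication, and section 8.1 lists an acute psychotic episode as an example of an adverse event. Sessions run three times a week and events are sought before and after each one, so closeness in time to a session will be common. Section 8.4 also allows exercise to be modified so that a participant with a minor problem can continue. In such a case abatement on stopping may never be observed, which closes off *Probable* while *Definitely* stays open.

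At stake is the consistency of the relatedness record across three sites, and any later statement about events caused by stand-alone resistance training.

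**Working it through.** The plan states no figure to reproduce and no rate can be calculated. The check sets the two definitions side by side as logical conditions.

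**Inputs, all from section 8.5.2**
- T: the event follows a reasonable time sequence.
- D: it abates on discontinuation.
- E: it is not reasonably explained by the participant's clinical state.
- R: it reappears on reintroduction.

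**Definitions as written**
- *Probable* = T and D and E
- *Definitely* = T or R

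**Counting.** Four yes/no conditions give 2 × 2 × 2 × 2 = 16 combinations.

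| Set | Calculation | Combinations |
|---|---|---|
| *Definitely* | 16 minus the 4 with T and R both false | 12 |
| *Probable* | T, D, E all true; R free | 2 |
| *Probable* but not *Definitely* | T true already satisfies *Definitely* | 0 |
| *Definitely* with the clinical state explaining the event (E false) | 8 with E false, minus the 2 with T and R both false | 6 |

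So *Probable* lies wholly inside *Definitely*, the reverse of the intended order. Half of the *Definitely* combinations (6 of 12) are cases that the illness explains.

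**Would replacing the or with an and be enough?** T and R leaves 4 combinations, with D and E free. In 2 of the 4, E is false. The top grade would still admit events explained by the illness, so this is not sufficient.

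**Would simple nesting be enough?** T and D and E and R leaves 1 combination, inside *Probable*, so the order is restored. But it makes abatement mandatory. An injury witnessed during a session that persists after exercise stops would then fail both top grades. A second route is needed for it.

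**The two-route version.** Add W: a directly observed mechanism. Then *Definitely* = T and E and [(D and R) or W]. Five conditions give 32 combinations. With T and E true, 8 combinations of D, R and W remain: 4 have W true, and 1 more has W false with D and R both true. That makes 5 of 32, and E is true in all 5. Of these, 2 have D false (W true, R free). They are the lasting witnessed injuries, and they fall outside *Probable* by intention, because direct observation replaces abatement as evidence.

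**The case against.** The strongest defence is that the grades are not applied mechanically. Section 8.5.2 asks for clinical judgement and for alternative causes to be considered, naming the natural history of the disease. *Possible* is written for an event that either the clinical state or the intervention could have caused, which is where a psychotic fluctuation would naturally go. This stands to a point: misgrading is possible, not certain. It does not repair the wording. An investigator who follows the judgement clause and one who follows the grade definition can give the same event different grades.

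The defence is right about the reach of the problem. A reader might infer more than the protocol supports in three ways.

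- *That the safety comparison between arms is compromised.* Section 11.4 compares adverse-event rates without reference to relatedness, and sections 6.1.1 and 8.3 record all events from consent whatever their cause. Grading does not alter that comparison, and the safety result as a whole remains interpretable.
- *That a decision in the trial turns on the grade.* Feasibility rests on recruitment, retention and participation. Withdrawal by the investigator (9.2) does not refer to causality. Insurer notification (16.5) also applies where causality cannot be excluded, a lower bar than either top grade. The wording on direct results in 6.1.1 is not tied to the grades of 8.5.2.
- *That a stated share of coincidental events would be graded Definitely, since sessions are frequent.* The protocol gives no time window for a reasonable sequence, and any such share would leave out the judgement step. No rate can be derived.

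**Conclusion.** The inversion is real and follows from the text alone, with no numerical assumption. As written, *Definitely* is the less demanding of the two top grades, every *Probable* event also qualifies for it, and an event explained by the underlying illness can literally receive it. The counts of 12 against 2 out of 16 describe the definitions, not expected event frequencies.

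The consequence is limited to the grading of events and to what is reported as intervention-related. The primary feasibility outcomes and the all-cause adverse-event comparison are unaffected. This is a drafting error in a safety definition, worth correcting because the correction is small and the protocol expects background events of the kind that the wording lets through.

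**What to change.** In 8.5.2, reconcile the two definitions so that *Definitely* is at least as demanding as *Probable*. It should require a reasonable time sequence **and** no reasonable explanation by the participant's clinical state or another cause, **and** one of the following:

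- (a) abatement on stopping together with reappearance on reintroduction; or
- (b) a directly observed mechanism, such as an injury witnessed during a session, with no abatement required.

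In 6.1.1, state which of the 8.5.2 grades count as a direct result of the intervention, chosen so that witnessed injuries are included.

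The cost is a sentence or two in the protocol and matching guidance in the case report form. Any events already graded under the present wording would need to be checked against the new definition. The downside is that fewer events will reach the top grade. No treatment rule, endpoint or analysis changes.
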